## 5.2 Causality

The relationship of each SAE to the trial intervention must be determined by a medically qualified individual according to the following definitions:

**Unrelated:** Where an event is not considered to be related to the intervention. The adverse event is probably produced by the participant's clinical state or by other modes of therapy administered to the participant.

**Possibly related:** Although a relationship to the intervention cannot be completely ruled out, the nature of the event, the underlying disease, concomitant medication or temporal relationship make other explanations possible.

**Probably related:** The temporal relationship and absence of a more likely explanation suggest the event could be related to the intervention.

**Definitely related:** The known effects of the intervention, its therapeutic class or based on challenge testing suggest that the intervention is the most likely cause.

All SAEs labelled possibly, probably or definitely related will be considered as related to the intervention.

### 5.3 Procedures for Recording Adverse Events

We do not anticipate any AEs to result as part of the intervention and as a result AEs will not be recorded.

### 5.4 Reporting Procedures for Serious Adverse Events

All SAEs that occur from randomisation until the end of the participant's 26-week follow up period, either observed by the recruiting clinician or reported by the participant, will be recorded and forwarded to PC-CTU, using the PC-CTU SAE Report form following assessment for seriousness and relatedness by the site clinician. This form will be completed and sent to PC-CTU using secure email or other secure methods as outlined on the report form. As a minimum, the following information will be recorded:

- Description
- Date of onset
- End date
- Severity
- Assessment of relatedness to study intervention
- Other suspect drug or device
- Action taken

Follow up information should be provided as necessary. SAEs must be reported to the PC-CTU within 24 hours of discovery or notification of the event. PC-CTU will be acting on behalf of the sponsor that is Oxford University.

The PC-CTU will acknowledge receipt of the SAE Report Form using the relevant PC-CTU documentation. This receipt will be emailed and faxed to the site clinician. If the site clinician does not receive a receipt within 24hrs of them sending the report (during office hours), they should re-send the SAE Report Form to the PC-CTU by email or fax and telephone ahead.

The documentation will be reviewed by members of the Trial Management Group and the 'SAE Checklist' will be completed and retained by the PC-CTU. Following the initial check of the report, any additional information will be requested, and the CI or their medically qualified designated representative will review and evaluate the report for seriousness, causality and expectedness. The Data Monitoring Committee (DMC) will agree prospectively how SAE reports will be reviewed.

Additional information, as it becomes available, will also be reported on the paper SAE Report Form (i.e. updating the original form) and returned to the PC-CTU. The SAE Report Form will be filed in the Trial Master File according to the relevant PC-CTU Standard Operating Procedure (SOP), with copies filed in the patient's medical notes and the Investigator Site File (if the participant is recruited through a Primary Care recruiting site).

*SAEs will be monitored by the trial manager and any concerns identified will be immediately raised with the CI and may be tabled for discussion at the regular PC-CTU Management Committee meetings or referred to the trial's DMC for review. The DMC also monitors the*

frequency and pattern of events reported as part of its independent oversight of the trial. Reporting will only include SAEs that are attributed to trial intervention or participation in the trial, **Foreseeable and predefined SAEs, e.g. if hospital admission is expected, do not need to be reported. Additionally, we will not be recording SAEs that are related to diabetes or any other underlying medical conditions** (See section 12.1 above).

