| Adverse Reaction (AR) | 
An untoward and unintended response in a participant which is related to a participant using their mobile phone as part of this intervention.
 
"Response" means that a causal relationship between using a mobile phone as part of this intervention (i.e. to read messages) and an AE is at least a reasonable possibility, i.e. the relationship cannot be ruled out.
 
All cases judged by either the reporting medically qualified professional or the Sponsor as having a reasonable suspected causal relationship to the intervention qualify as adverse reactions.
 |

|                                                       |                                                                                                                                                                                                                                                                                                                                                                                                                                                                                                                                                                                                                                                                                                                                                                                                                                                                                                                                                                                                                                                                                                                                                                                                                                                                         |

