| Serious Adverse Event (SAE)                           | 
A serious adverse event is any untoward medical occurrence that:
 
 
• results in death
 
• is life-threatening
 
• requires inpatient hospitalisation or prolongation of existing hospitalisation
 
• results in persistent or significant disability/incapacity
 
• consists of a congenital anomaly or birth defect.
 
 
Other 'important medical events' may also be considered serious if they jeopardise the participant or require an intervention to prevent one of the above consequences.
 
N.B. The term "life-threatening" in the definition of "serious" refers to an event in which the participant was at risk of death at the time of the event; it does not refer to an event that hypothetically might have caused death if it were more severe.
 
N.B. In this trial, we will not be collecting SAEs for:
 
 
○ scheduled hospital visits
 
○ hospitalisation due to diabetes or any other underlying conditions
 
○ congenital anomalies or birth defects
 
○ any life-threatening medical occurrence that is not related to the intervention or participation in the trial
 
 |

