### **9.2 Trial Steering and Data Monitoring Committees**

This trial is a feasibility study and as such will not have a Trial Steering Committee (TSC) or Data Monitoring Committee (DMC). In preparation for a full-trial an independent Trial Steering Committee will be convened to review progress and provide advice to the investigators about all aspects of the future trial.

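### Sections 5.1, 5.2 and 5.4 give incompatible rules on which SAEs are recorded, and section 5.4 gives SAE oversight to a DMC that section 9.2 says will not exist

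*Protocol*

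**What the plan says.** **Recording, wide rule.** Section 5.4 opens with "All SAEs that occur from randomisation until the end of the participant's 26-week follow up period" being recorded and forwarded to the trials unit after the site clinician has assessed seriousness and relatedness. Section 5.2 agrees: "The relationship of each SAE to the trial intervention must be determined by a medically qualified individual according to the following definitions". Those definitions include an unrelated category.

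**Recording, narrow rule.** Section 5.4 ends differently: "Reporting will only include SAEs that are attributed to trial intervention or participation in the trial", and "we will not be recording SAEs that are related to diabetes or any other underlying medical conditions". It supports this by pointing back to a section 12.1.

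**Recording, third rule.** The SAE entry in section 5.1 lists what will not be collected: scheduled hospital visits, "hospitalisation due to diabetes or any other underlying conditions", congenital anomalies or birth defects, and life-threatening occurrences unrelated to the intervention or to participation.

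**Adverse reaction.** Section 5.1 first defines this as "An untoward and unintended response in a participant which is related to a participant using their mobile phone as part of this intervention". The same entry ends by counting every case with a reasonably suspected causal link to the intervention. Section 5.3 says that non-serious adverse events are not recorded.

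**Oversight.** Section 5.4: "The Data Monitoring Committee (DMC) will agree prospectively how SAE reports will be reviewed". It also lets concerns be referred to the DMC and has the DMC watch the frequency and pattern of events as independent oversight. Section 9.2 says that the trial "will not have a Trial Steering Committee (TSC) or Data Monitoring Committee (DMC").

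**The concern.** These are operating instructions. A site clinician who learns of a death or an emergency admission has to decide whether to complete a form within 24 hours, and the answer depends on which paragraph is read.

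The diabetes and underlying-condition exclusion matters most. The intervention aims to help people take their medicines as intended. Participants take glucose-, blood-pressure- or lipid-lowering treatment, alone or in combination (section 3.4.1.1). An admission for hypoglycaemia is a plausible harm of such an intervention, although the protocol does not say so. It is also an event that would readily be classed as related to diabetes. If some sites drop such events and others send them, a final statement of few or no related SAEs could reflect the rule each site followed and not what happened to participants. Because non-serious events are not recorded, the SAE form is the only event-reporting route the protocol describes.

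The DMC conflict leaves a separate gap. The method for reviewing SAE reports is to be agreed by a committee that will not be formed.

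**Working it through.** No arithmetic decides this point, so the check is a comparison of the text. The table applies each rule to the same event.

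| Event between randomisation and 26 weeks | 5.4 opening and 5.2 | 5.1 list | 5.4 close: attributed events only | 5.4 close: no underlying conditions |
|---|---|---|---|---|
| Death judged unrelated, not from an underlying condition | Recorded, graded unrelated | Not on the list, so collected | Not reported | Does not apply |
| Unscheduled admission judged unrelated, not from an underlying condition and not life-threatening | Recorded, graded unrelated | Not on the list, so collected | Not reported | Does not apply |
| Life-threatening event judged unrelated, not from an underlying condition | Recorded, graded unrelated | Not collected | Not reported | Does not apply |
| Diabetes-related admission judged possibly related | Recorded, graded possibly related | Not collected | Reportable | Not recorded |

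1. **The three scopes differ.** No row gives the same answer in every column that applies. In the first two rows, 5.1 keeps events that the close of 5.4 drops. The SAE definition in 5.1 lists death separately from life-threatening events, so the exclusion of unrelated life-threatening occurrences does not plainly cover deaths.

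2. **Reading the opening of 5.4 as already limited by 5.1 does not remove the conflict.** It settles the third row, but the first two still differ between 5.1 and the close of 5.4. The fourth row still has two opposite answers within the close of 5.4.

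3. **The fourth row follows from the protocol's own definitions.** Section 5.2 allows the possibly related grade where underlying disease or concomitant medication offers another explanation, and it counts possibly, probably and definitely related events as related. One event can therefore be related to the intervention and also to diabetes. Neither exclusion of underlying-condition events (5.1 or the close of 5.4) makes an exception for that overlap.

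4. **The cross-reference fails.** Section 12 is the publication policy and has no 12.1. The exclusions are in 5.1.

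5. **The adverse reaction entry has two tests.** Its first sentence requires a link to phone use. Its last sentence requires only a suspected causal link to the intervention. A response to message content is clearly included under the last sentence and doubtful under the first.

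6. **DMC tasks.** Section 5.4 gives the DMC three: agreeing how SAE reports are reviewed, receiving referrals, and independently monitoring event patterns. Under 9.2 none of these has an owner. Section 5.4 also names the trial manager, the Trial Management Group, the chief investigator or a medically qualified delegate, and the trials unit's management committee. None of these is described as independent, and none is asked to set the review method.

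**The case against.** The strongest reply is that this is a low-risk feasibility trial with no safety objective. Section 3.3.3 anticipates no harm and says the messages avoid requiring specific changes in management. Leaving out diabetes-related admissions is a declared choice, made in both 5.1 and 5.4. It could also be argued that recording and reporting are different steps: everything is recorded at first, and only attributed events go further.

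Part of this stands. A narrow collection rule can be proportionate here, and choosing one is not an error in itself. The distinction between recording and reporting could soften the conflict over unrelated deaths. But the protocol does not draw that distinction: 5.4 uses reporting for what sites send to the trials unit. Nor does it rescue the last exclusion, which is worded as not recording.

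A reader might infer more than the text supports:

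- **That related diabetes admissions are certain to be discarded before anyone judges causality, so that an excess in one arm could not be seen.** Section 5.4 has relatedness assessed before forwarding, and one closing sentence would keep such an event. The text points both ways. A healthcare utilisation record is also collected in both arms, although its content on admissions is not shown.
- **That adverse reactions cover only harm from handling a phone.** The last sentence of that entry is wider.
- **That hypoglycaemia is the main expected harm because a recent admission for it is an exclusion criterion.** The criterion gives no reason and covers hyperglycaemia as well.
- **That a bound on the event rate is lost.** The protocol makes no claim from zero events, so no such figure bears on the point.
- **That the main trial will inherit this system.** The protocol does not say so, and section 9.2 plans an independent steering committee for that trial.

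**Conclusion.** The point holds as two contradictions in the text. First, the SAE recording rule has three scopes that cannot all be followed, and a diabetes-related SAE judged possibly related is both reportable and not to be recorded. Second, three oversight tasks are assigned to a committee that the protocol says will not be formed. The adverse reaction definition and the reference to section 12.1 are smaller faults in the same text.

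The size is qualitative. No estimate, interval or sample size changes. What is affected is whether sites act alike and whether the SAE results can be interpreted. How many events would be handled differently cannot be worked out from the protocol. The judgement assumes that sites follow the protocol as written; a working instruction or SOP outside it may already settle the matter, but none is shown. Given the low risk and the absence of a safety objective, this should be fixed, but it does not undermine the trial's feasibility aims.

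**What to change.** 1. Rewrite sections 5.1, 5.2 and 5.4 to state one recording rule. Relatedness should be assessed before any exclusion applies, so that an SAE judged at least possibly related is not dropped because it also relates to diabetes or another condition. If unrelated events are to be left out, say so once, and state whether that includes unrelated deaths. If recording and onward reporting are meant to differ, define each.
2. Make the first and last sentences of the adverse reaction definition agree.
3. Replace the reference to section 12.1 with the correct section.
4. Reconcile 5.4 with 9.2: either name a body that will exist to set the review method, take referrals and monitor event patterns, or correct 9.2. The programme steering committee should not be assumed to fill this role, because it appears only in the abbreviation list, with no stated membership, independence or remit.
5. Optional: tabulate deaths and non-elective admissions by arm, from the 26-week record extraction or the healthcare utilisation record.

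Items 1 to 4 cost a protocol correction and a matching instruction to sites. Item 5 would probably need added data fields. The 26-week extraction comes either from a practice medical summary or from a notes-review form, and section 3.8.2 lists neither deaths nor admissions among the items. The content of the utilisation record is not shown.

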## 6 STATISTICS

### 6.1 Description of Statistical Methods

The analysis will be carried out once the final patient has completed their 26-week follow up. An intention to treat approach will be used, where all participants randomised will be included in the group to which they were allocated, regardless of intervention received. The results of the primary and secondary objectives will be presented descriptively using proportions and 95% confidence intervals.

The primary outcome will be the number of patients recruited and randomised as a proportion (with 95% confidence interval) of the target recruitment number.

Secondary outcomes, including loss to follow up (%), withdrawals (%) and completeness of data collection for various outcomes (%), will be presented overall and separately by treatment group.

Exploratory outcomes (changes in primary and secondary measures to be used in the main trial) will be analysed using an intention to treat approach. Continuous outcomes will be analysed using an analysis of covariance adjusting for minimisation factors. Results will be presented as a difference in means with 95% confidence interval. Binary outcomes will be analysed in a similar way using log binomial regression models (adjusting for minimisation factors). Results will be presented as relative risks with 95% confidence intervals.

A detailed statistical analysis plan will be prepared prior to data lock.

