| Study Participants                    | Cohort 1 - Patients aged ≥35 years with type 2 diabetes
Cohort 2 – Primary care health professionals                                                                                                                                                                |                                                                                                                                                                                         |
| Planned Sample Size                   | Cohort 1 - We aim to recruit 200 patients
Cohort 2 - We aim to recruit between 12 and 30 healthcare professionals based on considerations of data saturation                                                                                                        |                                                                                                                                                                                         |
| Follow up duration                    | Two years                                                                                                                                                                                                                                                              |                                                                                                                                                                                         |
| Planned Study Period                  | 01/09/ 2018 to 31/08/ 2021                                                                                                                                                                                                                                             |                                                                                                                                                                                         |
| 
ObjectivesOutcome Measures
 |                                                                                                                                                                                                                                                                        |                                                                                                                                                                                         |

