## 2 OBJECTIVES, STUDY PARAMETERS AND ENDPOINTS

### 2.1 Summary of objectives and outcomes

| Objectives                                                                                                                                                                                                                                                                                      | Outcome Measures                                                                                                                                                              | Time-point(s) of evaluation of this outcome measure                                                 |
|-------------------------------------------------------------------------------------------------------------------------------------------------------------------------------------------------------------------------------------------------------------------------------------------------|-------------------------------------------------------------------------------------------------------------------------------------------------------------------------------|-----------------------------------------------------------------------------------------------------|
| To test participant recruitment to trial and willingness to be randomised.                                                                                                                                                                                                                      | Recruitment against planned recruitment rates.

Number of people showing an interest and not proceeding or those who withdraw from the control group and give a reason. | End of recruitment period.                                                                          |
| i. To assess the feasibility of collection of clinical measurement data for the proposed 15-month clinical trial. (With particular interest in 15 months prior to trial entry or following trial entry measurement collection of participant's HbA1c, systolic blood pressure and cholesterol). | i. Completeness of data collection of HbA1c, systolic blood pressure and total to HDL cholesterol ratio.                                                                      | i. End of follow-up period.                                                                         |

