### 2.2.1 Primary outcome

The primary outcome of this feasibility study is the rate of recruitment and randomisation of participants to the trial. We will measure recruitment against planned recruitment rates for the proposed main trial and number of people showing an interest in the trial and not proceeding or those who withdraw from the control group and give a reason.

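### Section 6.1 puts a proportion's confidence interval on number randomised over the target of 200, whereas section 2.2.1 defines the primary outcome as a recruitment rate against the main trial's plan

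*Protocol*

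**What the plan says.** Section 2.2.1 of the protocol defines the outcome as a rate: "The primary outcome of this feasibility study is the rate of recruitment and randomisation of participants to the trial". It names the comparator: "We will measure recruitment against planned recruitment rates for the proposed main trial". It adds a second component, which covers the "number of people showing an interest in the trial and not proceeding" and control-group withdrawals who give a reason. The synopsis and the table in section 2.1 also speak of recruitment against planned rates, and section 2.1 gives the time point as "End of recruitment period".

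Section 6.1 states the analysis: "The primary outcome will be the number of patients recruited and randomised as a proportion (with 95% confidence interval) of the target recruitment number". It does not repeat the target. The synopsis gives it ("Cohort 1 - We aim to recruit 200 patients"), and section 6.2 uses the same 200, with 100 per group. Section 6.1 also says in general terms that the primary and secondary objectives will be summarised by proportions with 95% intervals, and it leaves further detail to a statistical analysis plan.

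The readable text gives no planned main-trial rate, no length for the recruitment period, and no expected number of practices or of people approached.

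**The concern.** There are two separate problems.

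- **What is measured.** A count over this trial's own target is not a rate, and it is not a comparison with the main trial's planned rate. If recruitment runs until 200 are enrolled, the measure returns 100% however long that took and however many people had to be reached.
- **The interval.** A confidence interval for a proportion needs a denominator of observed units, each of which succeeds or fails. The target is a planning figure. Nobody observes 200 people of whom some are randomised and the rest are not.

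The trial exists to tell the main trial whether and how fast it can recruit. An interval that is too narrow, on a measure that can hide speed, gives those planners false assurance on the outcome they most need.

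**Working it through.** **Inputs.** Target 200 (synopsis, section 6.2). Ratio with 95% interval (section 6.1). Study period "01/09/ 2018 to 31/08/ 2021" and two-year follow-up (synopsis). Section 6.1 names no interval method, so binomial is an assumption, taken as the natural reading of a proportion.

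**Step 1: reproduce the plan's own figure.** Section 6.2 gives 73.8% to 85.3% for 80% follow-up in 200. The exact (Clopper-Pearson) limits for x out of n are the 0.025 quantile of Beta(x, n − x + 1) and the 0.975 quantile of Beta(x + 1, n − x). With x = 160 and n = 200 they are 73.78% and 85.31%, which matches. That use is legitimate: 200 randomised people are each followed up or not.

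**Step 2: the same interval on number over target, against the interval for a count.** The exact Poisson limits for a count x are χ²(0.025; 2x)/2 and χ²(0.975; 2x + 2)/2. Dividing by 200 expresses them as a share of the target.

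| Randomised | Ratio | Exact binomial 95% | Poisson 95% for the count | Poisson as % of 200 |
|---|---|---|---|---|
| 160 | 80% | 73.8 to 85.3% | 136.2 to 186.8 | 68.1 to 93.4% |
| 180 | 90% | 85.0 to 93.8% | 154.7 to 208.3 | 77.3 to 104.2% |
| 200 | 100% | 98.2 to 100% | 173.2 to 229.7 | 86.6 to 114.9% |
| 209 | 104.5% | does not exist | 181.6 to 239.3 | 90.8 to 119.7% |

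At 160 the widths are 85.31 − 73.78 = 11.5 points and 93.4 − 68.1 = 25.3 points, a ratio of about 2.2. At 200 the lower binomial limit is 0.025^(1/200) = 98.2%, and a Wald interval has zero width because p(1 − p) = 0. Above 200, p(1 − p) is negative and the exact method returns nothing. The protocol states an aim of 200 and no cap, so an overshoot is possible.

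The Poisson column treats the window as fixed. If recruitment instead stops at the 200th participant, time is the random quantity and the upper limit uses 2x degrees of freedom in place of 2x + 2. That gives 228.7 rather than 229.7, so the conclusion is the same.

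**Step 3: what the ratio does with speed.** No recruitment period is given. The study period is 36 months, and 36 − 24 months of follow-up leaves at most about 12 months. This is an inference from the synopsis, not a stated plan. For 200 randomised, the monthly rate (exact Poisson 95%) over an assumed range is:

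- 6 months: 200/6 = 33.3 (28.9 to 38.3)
- 9 months: 200/9 = 22.2 (19.2 to 25.5)
- 12 months: 200/12 = 16.7 (14.4 to 19.1)

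Section 6.1 reports 100% in all three cases.

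**Step 4: what a real denominator would show.** The documents give no count of people interested or eligible, so these are assumed. If 200 came from 500 people, uptake is 40% (exact binomial 35.7 to 44.4%). From 1,000 it is 20% (17.6 to 22.6%). From 2,000 it is 10% (8.7 to 11.4%). Here the binomial interval is valid, because each person in the denominator was or was not randomised.

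**The case against.** Four points can be put on the other side.

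- **A fixed window.** If the recruitment period is set in advance, number over target at its close equals observed rate over planned rate. Section 2.1 evaluates the outcome when recruitment ends, and the timeline in Appendix B is a figure that is not shown, so a fixed length may exist. This stands. A reader might infer that the ratio can never measure a rate, and the documents do not support that. Three weaknesses remain: the planned rate would be this trial's own and not the main trial's, reaching 200 early still reads 100%, and the interval is wrong either way.
- **More than one component.** A reader might infer that the plan holds nothing but this ratio. It does not: section 2.2.1 also collects those interested but not proceeding, which gives randomised over expressed interest. It is listed only as a number, however, and section 6.1 sets out no specific analysis for it.
- **No method named.** Section 6.1 does not say binomial, so the figures above depend on that reading. But a different proportion interval would not turn the target into a sample.
- **Detail for the analysis plan.** This does not stand. Section 6.1 fixes numerator, denominator and interval, so an analysis plan could not follow both it and section 2.2.1.

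**Conclusion.** The point holds: section 6.1 does not analyse the outcome that section 2.2.1 defines, and it attaches an interval that has no sampling meaning. On the binomial reading the interval is less than half the width of the Poisson one at 160, is falsely tight at 200, and does not exist beyond 200. The Poisson comparison assumes independent arrivals. Variation between practices would widen it further.

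How far the ratio hides speed depends on whether the window was fixed, which the readable text leaves open. The monthly rates and uptake figures are illustrations over assumed ranges.

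A reader might take this as a flaw that undermines the trial. The documents do not support that. The primary result is descriptive, with no test and no stop/go threshold resting on the interval, and the data for a correct analysis arise in the normal running of the trial. It should be fixed before the analysis plan is final.

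**What to change.** Replace the primary-outcome sentence in section 6.1, and carry the change into the analysis plan, so that it specifies:

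1. Participants randomised per month of recruitment, with a Poisson 95% interval, compared with the planned main-trial rate stated as a number. The start and end of the recruitment period should be stated. The sponsor must supply the planned rate, because the protocol does not give it.
2. Randomised over expressed interest, and randomised over eligible at screening, each with a binomial 95% interval. The first uses the interested-but-not-proceeding count already in section 2.2.1. Each person should be counted once, since section 3.5.2 allows some to be screened again.
3. Number randomised over 200 as a plain description, without an interval.

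Rates per practice and per invitation are optional. They would help in scaling to the main trial, but the protocol does not describe logging practice opening dates or mail-out counts, and mail-out is only one of several recruitment routes in section 3.5.1.

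The cost is wording. Interest and eligibility are handled by the trial team (sections 3.5.1 and 3.5.2), and randomisation is web-based (section 3.7), so items 1 and 2 need no new participant contact. The downside is a wider reported interval.
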